### Sample size and power

A sample size of 15 RACFs provides 86% power to detect a standardised effect size of 0.5 in change between pre-intervention and post-intervention period measures. This is under the assumptions that an analysis approach at the margins incorporating all pre- and post- intervention measures will be employed, that there will be the correlation across the three pre-intervention within sites of *r* = 0.5 and the correlation across the three post-intervention measures within sites of *r* = 0.25.

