**Methods:**

The Maximising Embedded Pharmacists in AGed CAre Medication Advisory Committees (MEGA-MAC) trial will be conducted in partnership with RACFs operated by three aged care provider organizations across four states of Australia. The intervention will involve knowledge broker dyads (pharmacist plus a MAC representative [e.g. nurse]) developing, implementing and evaluating RACF-specific local action plans to implement the Guiding Principles in up to 15 RACFs. Knowledge broker dyads will be supported by a national quality improvement collaborative (MEGA-MAC collaborative) comprising clinical experts, implementation scientists and resident and caregiver representatives. An interrupted time series design will be used to assess change over time with three pre-intervention (-6, -3 and 0 months) and three post-intervention assessment time points (+ 3, + 6, + 9 months). The primary outcome will be change in pre/post RACF-level concordance with the Guiding Principles measured using quality indicators (score 0 to 28, higher scores = greater concordance). A net benefit analysis will be conducted to examine the relative costs and benefits of implementing the intervention.

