## Analysis plan

### Effectiveness analysis

The primary analysis will employ a linear mixed model approach to investigate the effect of commencement of the intervention on the composite primary outcome. It will include treatment period (pre-intervention vs post-intervention) as a fixed, binary factor in the model; trial month as a continuous, fixed factor; and individual site as a random effect nested within the random effect of a MAC. An additional analysis will be presented that is the same as that described above but includes an interaction term between the treatment period and trial month factors. This is important as: i) there may be a natural underlying trend for facilities to increase in concordance with the Guiding Principles during the control period as a result of other background quality improvement processes; and ii) the intervention may not have an immediate effect on outcome domains being measured, but one that grows over time. We therefore have a conditional hypothesis that needs to be considered concurrently with our primary hypothesis to aid appropriate interpretation of results. This problem is analogous to that of interpretation of main effects and interaction effects arising from factorial trials. We will therefore follow recommendations for presentation of results of trials of this nature [41], and present both the models with and without the interaction term to allow comparison between the two.

Exploratory analyses to investigate the heterogeneity in treatment effects within sites and MACs will be undertaken by examining best linear unbiased predictions (BLUPs). This exploratory step is valuable, as an intervention that has highly variable impacts can be triangulated with our process evaluation to understand why the intervention may have had greater effect at some sites than others. This calculation will help to understand potential variation. Multiple imputation will be used to impute missing outcome values, where necessary.

All primary analyses will be conducted using the intention-to-treat (ITT) principle. Per protocol analysis will also be undertaken with the per protocol set including all RACFs without a major protocol deviation. Major protocol deviations may include, but are not limited to, the following:Loss of knowledge broker dyad (one or both members of the dyad); andIncomplete delivery of the intervention (e.g. local action plans, attendance at MEGA-MAC meetings).

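### The 86% power matches a pre/post comparison without a time term, but the primary model adjusts for trial month and has roughly 26–43% power for the same effect

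*Protocol article*

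**What the plan says.** Under *Sample size and power*, the article says: "A sample size of 15 RACFs provides 86% power to detect a standardised effect size of 0.5", the effect being the difference between the measures taken before and after the start of the intervention. The stated basis is that "an analysis approach at the margins incorporating all pre- and post- intervention measures will be employed", with a "correlation across the three pre-intervention within sites of *r* = 0.5" and "the correlation across the three post-intervention measures within sites of *r* = 0.25". No time trend is mentioned.

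Under *Effectiveness analysis*, the primary model is a linear mixed model with a binary period factor (before versus after the intervention), plus "trial month as a continuous, fixed factor; and individual site as a random effect nested within the random effect of a MAC". The period-by-month interaction belongs only to an additional analysis, so the linear month term is part of the primary model itself. The same section gives a possible background rise in concordance as a reason to consider time.

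Under *Data collection*, the assessments are at −6, −3, 0, 3, 6 and 9 months: three before and three after.

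**The concern.** The power statement concerns the difference between the pre and post measurements. The primary model estimates something narrower: the jump at the start of the intervention after a straight-line trend over the 15-month window has been removed. With only three equally spaced points on each side, much of a pre/post difference can be described equally well by that line, so the jump is estimated with far less precision than the difference in period means.

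If the 86% was computed without the month term, it is not a property of the primary analysis. A true 0.5 SD step would then more likely than not give a non-significant primary result, and anyone judging that result against 86% power would give it more weight than it deserves.

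**Working it through.** **Inputs from the article:** n = 15; effect 0.5 SD; correlation 0.5 among the three pre measures and 0.25 among the three post measures; months −6, −3, 0, 3, 6, 9; period and linear month both in the primary model.

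**Assumptions, because the article does not give them:** two-sided 5%; SD is that of a single facility-level measurement; pre/post correlation r between 0.25 and 0.5; the effect is an immediate, constant step. Power = Φ(0.5/SE − 1.96), with SE = √(V/15).

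**Step 1: reproduce 86% without month.**
- Variance of the pre mean = (1 + 2×0.5)/3 = 0.667. Variance of the post mean = (1 + 2×0.25)/3 = 0.500.
- Change in means: V = 0.667 + 0.500 − 2r. At r = 0.38, V = 0.407, SE = 0.165, power 86%. At r = 0.25, V = 0.667 and power is 66%. At r = 0.5, V = 0.167 and power is 99.7%.
- Baseline-adjusted: V = 0.500 − r²/0.667. At r = 0.25, V = 0.406 and power is 85.95%.

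So 86% is reachable in at least two ways, neither of which contains a time term.

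**Step 2: add linear month.**
- Period and month correlate at 0.878 over the six time points.
- The least-squares weights for the step, in time order, are 0.417, −0.333, −1.083, 1.083, 0.333, −0.417. Their sum of squares is 2.917 (1.458 on each side of the start), against 0.667 for a difference in means.
- The pre weights sum to −1 and the post weights to +1, so the contrast lies wholly within facility. A random intercept for facility or MAC therefore does not change its variance.

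With the stated correlations, V = (0.5×1.458 + 0.5) + (0.75×1.458 + 0.25) − 2r = 2.573 − 2r.

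| r (pre/post) | V, month-adjusted | SE | Power | V ratio to change in means |
|---|---|---|---|---|
| 0.25 | 2.073 | 0.372 | 27% | 3.1 |
| 0.38 | 1.813 | 0.348 | 30% | 4.5 |
| 0.50 | 1.573 | 0.324 | 34% | 9.4 |

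With one common correlation ρ, V = 2.917(1 − ρ):
- ρ = 0.25: V = 2.188, power 26%.
- ρ = 0.375: V = 1.823, power 30%.
- ρ = 0.5: V = 1.458, power 36%.

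Simulation with 20,000 replicates per scenario gave 26% to 36% for the month-adjusted model.

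**Step 3: let correlation decay with time.** Under a first-order autoregressive pattern with adjacent correlation 0.6, the three pre measures have average correlation (2×0.6 + 0.36)/3 = 0.52, close to the stated 0.5. V is 1.259 with the weights above, or 1.183 with fully efficient weighting, giving power of 41% and 43%.

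**Step 4: effect detectable at 86% power.** This is (1.960 + 1.080)×SE = 3.04×SE. Over the flat-correlation cases it runs from 3.04×√(1.458/15) = 0.95 SD to 3.04×√(2.188/15) = 1.16 SD.

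**Step 5: what would rescue 86%?** The within-facility variance 1 − ρ would have to be (0.5/3.04)²×15/2.917 = 0.139, that is, a common correlation of about 0.86. The stated values are 0.5 and 0.25.

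**The case against.** The best defence is that these figures rest on inputs the article does not state: the significance level, the pre/post correlation, the correlation pattern and the shape of the effect. That is right, and it limits how exactly the power can be quoted. Decaying correlation gives 41–43%, outside the flat-correlation range, because the step estimator leans most heavily on months 0 and +3, which are then the better correlated pairs. The direction does not depend on these choices: none of the cases examined approaches 86%, and a one-sided 5% test reaches only 37–48% under the flat correlations.

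Several stronger readings are tempting but not supported:
- **That the 86% is an arithmetic error, or is known to come from a simple difference in means.** It can be reproduced, and by more than one route. The article does not say which was used.
- **That adding month always multiplies the variance by 4.375.** That factor (2.917/0.667) holds only under one common correlation. The stated unequal correlations give 3.1, 4.5 or 9.4, depending on r.
- **That omitting the pre/post correlation is itself a fault.** An article may leave such an input to the full protocol or analysis plan.
- **That quoting power at 15 facilities misleads because the plan is** "to implement the Guiding Principles in up to 15 RACFs". The power sentence is expressly conditional on 15, and no smaller expected number is given.

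It can also be said that the plan anticipates background trend and delayed effects and will present models with and without the interaction. That helps interpretation, but both of those models contain month, so it does not make the 86% apply to either.

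**Conclusion.** The point stands as a mismatch between the basis of the power statement and the primary model. The 86% is recovered only without a time term, whereas the period effect in the primary analysis is adjusted for linear month. For a 0.5 SD step with 15 facilities, power in that model is about 27–34% under the stated correlations with a pre/post correlation of 0.25–0.5, 26–36% under a common correlation of 0.25–0.5, and about 41–43% under the autoregressive pattern. The detectable effect at 86% power is roughly 0.95–1.16 SD under the flat-correlation assumptions.

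All of this assumes two-sided 5% and an immediate constant step. The step assumption is a favourable one. If the effect grew as 0.25, 0.50, 0.75 SD (mean 0.5), the expected period coefficient would be 1.083×0.25 + 0.333×0.50 − 0.417×0.75 = 0.125 SD, because the month term absorbs most of the growth. The article itself allows that the effect may grow.

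A reader might infer that the month term should be dropped or that the trial must recruit more facilities. Neither follows. The model's reason for including month is sound; it is the stated power that does not belong to it.

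**What to change.** Do one of two things in *Sample size and power*:
- Recompute and restate the power, or the detectable effect, for the month-adjusted primary model, using the sponsor's own correlation assumptions, including the correlation between pre and post measures.
- Or keep the 86% and say explicitly that it applies only to a pre/post contrast without the month term, and not to the primary analysis.

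The ranges above show the size of the problem; they are not figures for the sponsor to adopt. The cost is one recalculation and a sentence or two of rewording, with a less favourable stated figure. No extra facilities and no change to data collection or to the primary model are needed.

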## Analysis plan

### Effectiveness analysis

The primary analysis will employ a linear mixed model approach to investigate the effect of commencement of the intervention on the composite primary outcome. It will include treatment period (pre-intervention vs post-intervention) as a fixed, binary factor in the model; trial month as a continuous, fixed factor; and individual site as a random effect nested within the random effect of a MAC. An additional analysis will be presented that is the same as that described above but includes an interaction term between the treatment period and trial month factors. This is important as: i) there may be a natural underlying trend for facilities to increase in concordance with the Guiding Principles during the control period as a result of other background quality improvement processes; and ii) the intervention may not have an immediate effect on outcome domains being measured, but one that grows over time. We therefore have a conditional hypothesis that needs to be considered concurrently with our primary hypothesis to aid appropriate interpretation of results. This problem is analogous to that of interpretation of main effects and interaction effects arising from factorial trials. We will therefore follow recommendations for presentation of results of trials of this nature [41], and present both the models with and without the interaction term to allow comparison between the two.

Exploratory analyses to investigate the heterogeneity in treatment effects within sites and MACs will be undertaken by examining best linear unbiased predictions (BLUPs). This exploratory step is valuable, as an intervention that has highly variable impacts can be triangulated with our process evaluation to understand why the intervention may have had greater effect at some sites than others. This calculation will help to understand potential variation. Multiple imputation will be used to impute missing outcome values, where necessary.

All primary analyses will be conducted using the intention-to-treat (ITT) principle. Per protocol analysis will also be undertaken with the per protocol set including all RACFs without a major protocol deviation. Major protocol deviations may include, but are not limited to, the following:Loss of knowledge broker dyad (one or both members of the dyad); andIncomplete delivery of the intervention (e.g. local action plans, attendance at MEGA-MAC meetings).

Data will be analysed using Stata (StataCorp, College Station, TX), SAS (SAS Institute, Cary, NC) and the Statistical Package for the Social Sciences (SPSS, Inc., Chicago, IL).

### Economic analysis

A net benefit analysis will be conducted to examine the relative costs and benefits of implementing the intervention. We will model the results of the economic evaluation over several perspectives, including the perspective of the RACF, the Australian government as the funder of health and aged care and from a societal perspective. With each of these perspectives, we will vary the assumptions of who would be the payer of the program, with one set of models looking at if the RACFs was paying for the program directly, and another where the government would pay.

Modelling of cost data is required in this evaluation and economic assumptions will be made. Costs will include the direct costs of the intervention (e.g. salary costs of the knowledge broker) and downstream costs (e.g. staff time preparing for MAC meetings). Benefits will consider the monetised impact of hospitalisations and medication incidents. Measurement and valuation of activity will either be collected internally from the trial budget (e.g. salary costs of the knowledge broker) or valued using market rates (e.g. national or state-based awards as relevant) or by extrapolation based on previously published work for costs from external sources (e.g. the cost of staff to attend a MAC). The mean (Standard Deviation) will be presented for the cost of the intervention, downstream costs, cost of medication incidents and hospitalisations. To overcome variability in resident numbers at each of the RACFs included in the trial, the cost of the intervention, downstream costs, and costs of medication incidents and hospitalisations will be presented per bed at the RACF. Cost data will be presented in Australian dollars (AUD). Costs will be inflated accordingly by consumer price index (CPI) and presented as a consistent base year (e.g. 2025/2026 financial year).

### Process evaluation

A mixed method process evaluation will be undertaken using the Consolidated Framework for Implementation Research (CFIR) [42, 43]. Process evaluation will be performed through an analysis of qualitative data (e.g. local action plans, goals for improvement, interviews, anonymous MEGA-MAC meeting online surveys) and quantitative measures of engagement with the intervention (e.g. attendance to MEGA-MAC meetings, percentage of training completed by knowledge broker dyads). Data will be de-identified and qualitatively analysed to inform on outcomes relating to local process evaluations, barriers and enablers to change and feasibility and acceptability of the MEGA-MAC model for guideline implementation.

**Dissemination.**

Findings will be disseminated through lay summaries, conference presentations, and peer-reviewed publications in open access journals. The lay summaries will be developed in partnership with the three participating aged care provider organisations and the Project Interest Holder Group. All participating RACFs, MACs, and aged care provider organisations will be provided a final report summarising key findings. Research findings will also be disseminated through member organisations of the MEGA-MAC Project Interest Holder Group and their professional networks.

## Discussion

The MEGA-MAC trial investigates a novel system-level role for onsite aged care pharmacists to support close working relationships with their RACF and MAC to drive local collaborative medication-related quality improvement initiatives. The study will establish a national real-time clinical network for onsite aged care pharmacists and MAC representatives to share experiences and support residential aged care provider organisations to maximise the function of their MACs and implementation of the Guiding Principles into their RACFs. This study directly addresses national and international priority areas and the need for new models of guideline implementation to promote safe and effective medication use.

This trial will be the first to evaluate the novel role of a knowledge broker dyad to support guideline implementation in RACFs. The dyad aspect of the intervention makes this trial distinct from previous research [25] and was chosen to ensure the dyad would collectively have a strong understanding of the evidence being translated (the Guiding Principles – pharmacist), and a strong understanding of the context in which it is to be applied (the RACF – MAC representative). The inclusion of a pharmacist as part of the dyad is consistent with the Royal Commission into Aged Care Quality and Safety’s recommendation for pharmacists to have greater involvement with RACFs and the Australian Government funding for onsite aged care pharmacists [24, 44]. Clinical governance and quality use of medication are two of the five key roles of the new aged care onsite pharmacist model that commenced in July 2024 [45]. This trial will build evidence as to how pharmacists can work collaboratively in a system-level capacity. The MAC representative in the dyad brings an understanding of the RACF-, MAC- and aged care provider organisation-level context. They will facilitate organisational support and effective collaboration within interprofessional teams which are known facilitators associated with the success of embedded on-site aged care pharmacists [24, 46, 47]. Additionally, the national quality improvement collaborative builds on evidence of success in other settings [16, 20] and provides peer and expert support to address known challenges for health care professionals in RACFs such as ‘isolation’, inconsistent practices and lack of sharing of best-practice [12, 24, 46].

Knowledge brokers utilise a series of evidence-based knowledge translation strategies to support guideline implementation including staff training, audit and feedback and local action planning [15, 47]. The ability of the knowledge broker intervention to adapt to the local context is a key strength, however, gaining insight into the specific activities knowledge brokers undertake is essential for informing future scale-up efforts. The MEGA-MAC trial will generate important evidence on the roles of a knowledge broker through a comprehensive process evaluation guided by CFIR, while also assessing cost-effectiveness using a net-benefit analysis. This will enable resource modelling and projections and support the potential expansion and broader implementation of knowledge brokers in RACFs.

The MEGA-MAC intervention represents a transformative, system-level multi-faceted knowledge translation strategy that will generate critical insights on the role of knowledge brokers, MACs and quality improvement collaboratives for supporting guideline implementation and medication management in RACFs. The findings from this trial have the potential to inform future policy, define new roles for healthcare professionals, drive sustainable improvements in medication safety, and serve as a model for enhancing clinical governance in aged care and beyond.

## Data Availability

Not applicable.

## Abbreviations

AHPRA: Australian Health Practitioner Regulation Agency
ANZCTR: Australian and New Zealand Clinical Trial Registry
DCT: Data collection tool
KB: Knowledge broker
IHI: Institute for Healthcare Improvement
MAC: Medication advisory committee
MEGA-MAC: Maximising Embedded Pharmacists in Aged Care Medication Advisory Committees
NHMRC: National Health and Medical Research Council
NSW TAG: New South Wales Therapeutic Advisory Group
NQIP: National Quality Indicator Program
PDSA: Plan, do, study, act
RACF: Residential aged care facility
REDCap: Research Electronic Data Capture
SMART: Specific, measurable, achievable, relevant, timely.
SPIRIT: Standard Protocol Items: Recommendations for Interventional Trials
QCE-ACC: Quality of Care Experience Aged Care Consumers
QoL: Quality of Life
QOL-ACC: The Quality of Life Aged Care Consumers
WHO: World Health Organization
